### Data Management and Statistical Analysis

A baseline comparison using both student t-tests and chi-square for equal proportions of demographic data will be done between groups at enrolment. Data will be analyzed using SPSS Version 17.0. The distribution, range of scores and heterogeneity will be examined for participants in both groups. Mean changes scores, standard deviations and 95% confidence intervals will be calculated and specific analysis detailed under each outcome measure will be performed. Repeated measures, between/within analysis of variance (ANOVA) will be performed to investigate for the main effects of time and group. Post hoc analyses will then be performed to ascertain where the differences occur. A Bonferroni correction will be used as the post hoc measure as there are multiple outcome measures. Analysis will be by both intention-to-treat and per-protocol method. Any violations of the protocol will be noted. Statistical significance will be set at p < 0.05 and p < 0.025(two-tailed). All efforts will be taken to avoid missing data but if it occurs a carry forward imputation will be done and linear mixed modelling will be used for overall analysis. Reasons for loss of follow up will be recorded.

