### Recruitment, Randomisation and Blinding

Eligible patients will be identified and consent will be sought by the chief and principal investigators, with next of kin or substitute decision maker. Participants recruited will be randomized into control and intervention arms using computer generated randomization; http://www.randomization.com/. The randomization sequence will be generated and re-identifiable serial numbers will be assigned by a research personnel not involved in the study. They will be concealed from consent designee research staff for group allocation to prevent selection bias and protected by an electronic password. Participants, substitute decision makers and outcome assessors will be blinded to group allocation to avoid influence over treatment effect. Blinding of the treating physiotherapist and health care providers cannot be ensured due to the nature of the research intervention.

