### Demographics

Patient demographic information will be collected at baseline (recruitment) and ICU and hospital discharge and will include; age, gender, primary reason for readmission to ICU, Acute Physiological and Chronic Health Evaluation II (APACHE II)[58], Sequential Organ Failure Assessment (SOFA) score [59], Charlson Comorbidity Index [60], time on mechanical ventilation, length of ICU and hospital stay, readmissions to ICU and 90-day mortality.

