### Primary Outcome Measures

All primary outcomes will be measured at baseline (recruitment) and at ICU discharge and quality of life at 6 months post hospital discharge. The primary outcome measures will report the level of physical functioning and quality of life (long-term effects) of the participants. Physical function will be measured using the Acute Care Index of Function (ACIF) and the Physical Function ICU Test (PFIT).

The ACIF will essentially rate simple physical function (transfer bed to chair, sit to stand independently) of the patient on leaving the ICU [62]. The PFIT is a newly developed clinical tool for testing functional strength and endurance capacity in ICU patients. It consists of a battery of tests assessing endurance, muscle strength, cardiovascular capacity and functional ability which are domain representative of physical function and specific for the use of higher functional assessment in the critically ill [63]. These have been chosen as corresponding measuring instruments as they have demonstrated reliability, validity and responsiveness in the ICU population [63,64].

Quality of life will be measured using the Short Form-36 (SF-36) Health Survey Questionnaire. Information from the next of kin will be used to provide proxy scores which have been demonstrated to have good reliability and validity [65].

The constructs of psychological well being will be measured using the anxiety subscale of the Hospital Anxiety and Depression Scale (HADS) as psychological wellbeing is known to be highly correlated to functional physical outcomes [66].

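### Baseline significance tests between randomised groups are uninformative, and the stated outcome model leaves the recruitment severity scores unused, which gives up precision though not validity

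*Protocol article*

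**What the plan says.** Four places in the protocol article bear on this point.

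- **Demographics.** "Patient demographic information will be collected at baseline (recruitment) and ICU and hospital discharge". The list includes age, APACHE II, SOFA and the Charlson index.
- **Recruitment, Randomisation and Blinding.** "Participants recruited will be randomized into control and intervention arms using computer generated randomization". No stratification by severity is mentioned.
- **Data Management and Statistical Analysis.** For baseline data: "A baseline comparison using both student t-tests and chi-square for equal proportions of demographic data will be done between groups at enrolment". For outcomes: "Repeated measures, between/within analysis of variance (ANOVA) will be performed to investigate for the main effects of time and group". The section adds "Mean changes scores, standard deviations and 95% confidence intervals will be calculated" and, in the sentence on missing data, "linear mixed modelling will be used for overall analysis". No covariate is named for any of these analyses, and nothing is said about what would follow from a significant or non-significant baseline test.
- **Primary Outcome Measures.** "All primary outcomes will be measured at baseline (recruitment) and at ICU discharge". A baseline value of the outcome is therefore planned.

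**The concern.** In a randomised trial the hypothesis behind a baseline test is that the two groups come from the same population. Randomisation makes that true, so the test can only produce correct non-rejections and false alarms. Its p-value does not measure whether an observed difference matters for the outcome either. That depends on the size of the difference and on how strongly the variable predicts the outcome.

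Meanwhile the variables that could explain outcome variation are collected and then given no stated role in the outcome analysis. What is at stake is efficiency. If age and severity predict physical function at ICU discharge, leaving them out makes the standard error of the treatment effect larger than it need be. This matters most if the number of evaluable patients falls towards the stated minimum of 35 per group, where there is little or no spare power.

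**Working it through.** **Inputs from the protocol article (Sample size; Data Management and Statistical Analysis).** Minimum n = 35 per group; effect size 0.7, read as a standardised difference; 80% power; two-tailed significance at 0.05 and at 0.025 (Bonferroni); 126 per group to be recruited.

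**Input not in the document.** The correlation r between the covariates and the outcome (for several covariates, their multiple correlation). Assumed values: 0.2, 0.3 and 0.5.

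**Step 1: reproduce the plan's figure.** n per group = 2(z₁₋α/₂ + z₀.₈)² / 0.7².

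- α = 0.05: 2(1.960 + 0.842)² / 0.49 = 32.04, so 33 (34 with the t distribution). This is within two patients of the stated 35.
- α = 0.025: 2(2.241 + 0.842)² / 0.49 = 38.8, so 39 (41 with the t distribution). The stated 35 does not reach this.

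The 35 is therefore consistent with an unadjusted two-group comparison at two-sided 0.05.

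**Step 2: power without adjustment at 35 per group.** The standard error in SD units is √(2/35) = 0.239, and 0.7/0.239 = 2.928.

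- α = 0.05: Φ(2.928 − 1.960) = 83.4%.
- α = 0.025: Φ(2.928 − 2.241) = 75.4%.

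**Step 3: power with adjustment.** The residual SD becomes √(1 − r²), so power = Φ(2.928/√(1 − r²) − z₁₋α/₂). The last two columns give n per group for 80% power.

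| r (assumed) | √(1 − r²) | 2.928/√(1 − r²) | Power, 0.05 | Power, 0.025 | n, 0.05 | n, 0.025 |
|---|---|---|---|---|---|---|
| none | 1.000 | 2.928 | 83.4% | 75.4% | 33 | 39 |
| 0.2 | 0.980 | 2.989 | 84.8% | 77.3% | 31 | 38 |
| 0.3 | 0.954 | 3.070 | 86.6% | 79.6% | 30 | 36 |
| 0.5 | 0.866 | 3.381 | 92.2% | 87.3% | 25 | 30 |

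The gain is 1.4, 3.2 and 8.8 percentage points at 0.05, and 1.9, 4.2 and 11.9 points at 0.025.

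**Step 4: what the baseline test can tell.** The largest observed standardised difference that stays non-significant at 0.05 is t₀.₉₇₅ × √(2/n). With 35 per group this is 1.995 × 0.239 = 0.48 SD; with 126 per group it is 0.25 SD. The same observed gap of 0.3 SD would be non-significant in the smaller set and significant in the larger one, though its relevance to the outcome is unchanged. The p-value reflects sample size as much as imbalance.

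**Step 5: does the unadjusted outcome test lose its type I error?** No. With baseline and outcome bivariate normal, averaging over all randomisations gives 5.0% at nominal 5%. Averaging only over randomisations in which the baseline test is non-significant (|z| < 1.96) gives between 4.3% and 4.8% for r from 0.5 down to 0.3, slightly below nominal.

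**The case against.** The strongest reply has four parts.

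1. **The article is condensed.** It names a mixed model without listing its terms, and it points to analyses specific to each outcome. Covariate lists are often left to the full protocol or SAP, which are not shown, and naming time and group does not exclude covariates. This stands as a limit: one cannot say that adjustment is ruled out. It does not rescue the baseline tests, which the article states outright.
2. **The baseline outcome value already enters** through change scores and repeated measures. This also stands. The calculation above compares a single-time-point analysis with and without covariates, so what severity adds beyond the baseline outcome value could be smaller. One may suspect that recruitment scores in ventilated patients sit near the floor and predict little, but the document gives no data on that.
3. **The correlations are assumed.** The article gives no figure linking age, APACHE II, SOFA or Charlson to ACIF or PFIT. At r of 0.3 or less the gain is only about 1 to 4 points.
4. **An unadjusted randomised comparison is valid.** Correct, and not disputed here.

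A reader might also infer three stronger claims that the document does not support.

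- **That a non-significant baseline test will be taken as proof of comparability.** No decision is attached to the tests.
- **That the unadjusted result is biased or its type I error inflated.** Higher error rates appear only if one conditions on an imbalance close to the significance limit; step 5 shows the overall rate is held. Chance imbalance is imprecision that the confidence interval already reflects.
- **That only 35 of every 126 patients are expected to be evaluable.** The 35 is a stated minimum, and the projection to 126 also allows for refusals, which may come before randomisation.

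**Conclusion.** The point holds as one of method and efficiency. The baseline tests are uninformative and should go. As written, the outcome analysis makes no stated use of age and the three severity scores collected at recruitment. Adjusting for them would be worth about 2 to 12 percentage points of power at two-sided 0.025, and about 1 to 9 points at 0.05, for correlations of 0.2 to 0.5.

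This range rests on 35 evaluable patients per group, an effect of 0.7 SD, a normal approximation, a single-time-point comparison and correlations that the document does not supply. If many more than 35 per group are evaluable, power for 0.7 is already high and the benefit is mainly a narrower confidence interval. Validity of the unadjusted comparison is not in question.

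**What to change.** 1. Delete the t-tests and chi-square tests of baseline data. Present a descriptive table by group (means and SDs or medians and ranges; counts and percentages), once for all randomised patients and once for those with an ICU-discharge ACIF or PFIT.
2. In the linear mixed model already planned, prespecify age and the recruitment values of APACHE II, SOFA and the Charlson index as fixed covariates. Include them whatever imbalance is observed, so that the choice cannot depend on the data. Use only recruitment values, since the demographic data are also collected at discharge.
3. If a full SAP already lists covariates, align the two documents.

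The cost is wording only, as every variable is already collected. The downside is three or four degrees of freedom. With all four entered as single linear terms in a comparison of 70 patients, the residual degrees of freedom go from 68 to 64, which is negligible.

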### Sample size

Clinically important difference and the standard deviation estimates used in our sample size calculations were based on a previous clinical trial [64]. Sample size was calculated using the ACIF [62] for hypothesis testing with a type I error rate of 0.05 and 0.025 with Bonferroni adjustment and type II error rate of 0.20 (80% power). A minimum of 35 per group (70 total) is required to detect a minimum clinical difference (effect size) of 0.7 for physical functional outcomes which will yield clinically significant results for the main hypothesis achievable by intervention. Projection of the sample size after adjusting for attrition or withdrawal rates, participation refusals and possible death due to sepsis; based on admission and mortality rates in the RBWH ICU, 126 patients per group (252 in total) will be required.

A smaller number of patients will undergo mtDNA, tissue oxygenation and microcirculatory measurements as these will be tested as pilot investigations. To test these secondary hypotheses, a minimum of 58 per group is required to detect a minimum clinical difference of 0.8 for clinically significant changes in mitochondrial DNA [78], a minimum 91 per group is required to detect a clinical difference of 0.4 and 59 per group is required to detect a minimum clinical difference of 0.7 for clinically significant changes in tissue oxygenation [45] and microcirculation [46] respectively, all corrected for with Bonferroni adjustment of 0.025.

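### The repeated-measures ANOVA is aimed at the main effects of group and time; for ACIF and PFIT the group main effect estimates only half the effect at ICU discharge

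*Protocol article*

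**What the plan says.** Under Data Management and Statistical Analysis, the protocol article names the model and the effects it is meant to examine: "Repeated measures, between/within analysis of variance (ANOVA) will be performed to investigate for the main effects of time and group". The group-by-time interaction is not named, and neither is a comparison of discharge scores adjusted for baseline. The same paragraph mentions three other things: mean change scores with confidence intervals, post hoc analyses to locate differences, and a linear mixed model introduced alongside the handling of missing data. No between-arm test is attached to the change scores, no post hoc contrasts are listed, and the terms of the mixed model are not given.

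The section headed Primary Outcome Measures gives the visit schedule: "All primary outcomes will be measured at baseline (recruitment) and at ICU discharge and quality of life at 6 months post hospital discharge". ACIF and PFIT therefore have two measurements, the first before treatment. Quality of life has a third.

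The Sample size section is based on ACIF: "A minimum of 35 per group (70 total) is required to detect a minimum clinical difference (effect size) of 0.7". After allowance for refusals, withdrawal and death, "126 patients per group (252 in total) will be required".

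**The concern.** The primary hypothesis is that early rehabilitation improves physical function, and the Abstract places the primary physical function tests at discharge from ICU. In a randomised trial with one pre-treatment and one post-treatment measurement, that question is answered by the difference between arms at discharge, adjusted for baseline or expressed as a difference in change.

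Neither main effect answers it. The group main effect averages over visits, including one at which treatment cannot have acted. The time main effect only shows whether patients as a whole change between recruitment and discharge. The group main effect also adds any chance baseline imbalance to the estimate instead of removing it.

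The type I error rate is not the issue, because with no treatment effect the expected group main effect is also zero. Two other things are at stake. An estimate reported from the named effect would be half the size of the effect the trial was planned to detect. Depending on how much baseline scores vary, the test may also have less power than planned.

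**Working it through.** **Inputs from the article.** Standardised difference 0.7; 35 per group; 80% power; alpha 0.05, and 0.025 with Bonferroni, two-sided; two visits for ACIF and PFIT.

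**Assumptions, because the article gives neither.** k = baseline SD divided by discharge SD, taken as 0, 0.25, 0.5 and 1. ρ = baseline–discharge correlation, taken as 0, 0.3, 0.5 and 0.7. The true difference is 0 at baseline and 0.7 discharge SDs at discharge.

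**Step 1: the plan's own figure.** For a two-sample comparison of means at two-sided 0.05, n = 2(1.960 + 0.842)²/0.7² = 32.0. This rounds up to 33 per group, or 34 with the t distribution. The stated 35 is within 2 of these, and its power by the noncentral t is 82%. At two-sided 0.025 the requirement is 39 (normal) or 41 (t), which does not match 35. The figure therefore behaves like a plain two-group comparison at 0.05, and 82% is the benchmark below.

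**Step 2: what the group main effect estimates.** With two visits it is ½(baseline difference) + ½(discharge difference) = ½(0) + ½(0.7) = 0.35. This does not depend on k or ρ. With three equally weighted visits, as for quality of life, it is (0 + discharge difference + 6-month difference)/3, so baseline has weight one third.

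**Step 3: the standardised effect seen by the test.** The SD of a patient's two-visit mean is √[(1 + k² + 2ρk)/4]. Hence d = 0.35/√[(1 + k² + 2ρk)/4] = 0.7/√(1 + k² + 2ρk). With k = 1 and ρ = 0.5, d = 0.7/√3 = 0.404.

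**Step 4: power of the group main effect at 35 per group, two-sided 0.05 (noncentral t).**

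| Baseline SD / discharge SD | ρ = 0 | ρ = 0.3 | ρ = 0.5 | ρ = 0.7 |
|---|---|---|---|---|
| 1 | 53% | 43% | 39% | 35% |
| 0.5 | 73% | 64% | 59% | 54% |
| 0.25 | 80% | 75% | 71% | 68% |
| 0 (no spread) | 82% | 82% | 82% | 82% |

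In the last row the p-value equals that of the discharge comparison, but the estimate is still 0.35.

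A check with 20,000 simulated trials per correlation at k = 1 gave power of 44%, 38% and 35% at ρ = 0.3, 0.5 and 0.7. The mean estimate was 0.35 each time.

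**Step 5: the alternatives.**
- ANCOVA on the discharge score has d = 0.7/√(1 − ρ²) where baseline varies. Power is 82%, 86%, 92% and 98% at ρ = 0, 0.3, 0.5 and 0.7.
- The unconstrained group-by-time contrast (difference in change) has d = 0.7/√(1 + k² − 2ρk). At k = 1, power is 53%, 68%, 82% and 96%.
- At k = 1 and ρ = 0.5, the numbers per group for 80% power are 98 (group main effect), 34 (group-by-time contrast) and 26 (ANCOVA).

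**The case against.** **Baseline scores may hardly vary.** Eligible patients have been ventilated for at least 48 hours, and the first intervention stage is for sedated patients. ACIF rates tasks such as transfers and standing up. Scores at recruitment may well cluster at the floor, and then the power loss is small or nil. This stands. A reader might infer from the equal-SD row that the trial has only 35–43% power, but the documents do not support that. Those figures are the unfavourable end of a range resting on assumed values. The halving of the estimate is not affected.

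**The same paragraph plans more than main effects.** A between/within ANOVA normally prints the interaction. With two visits, the between-arm difference in mean change is the group-by-time contrast, and the mixed model could supply it too. So it would be wrong to infer that the right comparison will never be produced. What remains is that none of these is named as the treatment test, while the main effects are named as the target.

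**Gating.** A reader might infer that the right comparison is examined only if a main effect is significant. The article says only that post hoc analyses come afterwards and states no such condition.

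**A fuller plan may settle the contrasts.** That is a good answer to any complaint about missing model terms or covariates, and none is made here. It does not answer a stated target that is the wrong one.

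**The sample-size test is not stated.** Correct. That 35 comes from comparing two means is a reading supported by the arithmetic, not a declared fact.

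**Far more than 35 per group may be evaluable.** Power would then recover. At k = 1 and ρ = 0.5, 98 of 126 (78%) would be needed, whereas the plan's stated minimum is 35 of 126 (28%).

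**Conclusion.** The point holds for the stated target of the ANOVA. For ACIF and PFIT the group main effect estimates half the discharge difference, 0.35 instead of 0.70. This follows from the two-visit schedule and randomisation alone. For quality of life the dilution is milder, with one third of the weight on baseline if all three visits enter the model. The time main effect carries no information about treatment.

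The effect on power is conditional. At 35 per group, a 0.7 SD effect and two-sided 0.05, it ranges from about 35% to 82%, against 82% for a plain discharge comparison. The position in that range depends on the baseline SD and correlation, which the article does not give. The upper part is plausible in this population.

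A reader might also want to count the baseline significance tests, or the lack of adjustment for severity scores and age, as part of this fault. They are separate matters of practice: they do not alter what the group main effect estimates, and further covariates may be left to a fuller plan.

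**What to change.** State that the treatment test and estimate for ACIF and PFIT is the between-arm difference at ICU discharge, adjusted for the baseline score where that score varies, with a 95% CI. Either ANCOVA or the group-by-visit contrast of the planned mixed model will serve. If the mixed model is used, say whether the baseline means are constrained to be equal between arms. Without that constraint the contrast is the difference in change, which has less power than ANCOVA when the correlation is low (Step 5). Remove the main effects of group and time as the test of treatment. For quality of life, name the visit or visits at which the between-arm difference is the target.

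The cost is a change of analysis wording before the data are analysed. No new data, visits or patients are needed. Adjusting for further baseline covariates and replacing baseline p-values with descriptive tables are optional and not required by this point.

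### Holm's step-down procedure would give the same family-wise error control as the planned Bonferroni correction and more power: a cheap improvement, not an error

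*Protocol article*

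**What the plan says.** The Data Management and Statistical Analysis section of the protocol article plans a repeated-measures ANOVA with post hoc analyses, and then states: "A Bonferroni correction will be used as the post hoc measure as there are multiple outcome measures". It adds: "Statistical significance will be set at p < 0.05 and p < 0.025(two-tailed". It does not say which outcome is tested at which level, and it mentions no step-down method.

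The Sample size section uses the same pair of levels: "type I error rate of 0.05 and 0.025 with Bonferroni adjustment". The calculation rests on ACIF: "A minimum of 35 per group (70 total) is required to detect a minimum clinical difference (effect size) of 0.7 for physical functional outcomes". For recruitment, "126 patients per group (252 in total) will be required", a number reached "after adjusting for attrition or withdrawal rates, participation refusals and possible death due to sepsis".

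The family is not defined consistently. The abstract names ACIF and PFIT at ICU discharge as the primary outcome measures. The Primary Outcome Measures section also covers SF-36 and the HADS anxiety subscale. The primary hypothesis under Hypotheses and Aims joins physical function with quality of life.

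**The concern.** With two tests at an overall 5% level, Bonferroni holds each to 0.025 whatever the other shows. Holm compares the smaller p-value with 0.025 and, if that is significant, the larger with 0.05. The overall error guarantee is the same.

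ACIF and PFIT both measure physical function at ICU discharge. If the treatment works, both may well move, and this is the situation in which a single-step rule gives up most. At stake is the chance of a claim on each measure, and above all on both, if the evaluable number ends near the plan's minimum of 35 per group.

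**Working it through.** **Inputs from the article.** Standardised difference 0.7; 35 evaluable per group; 80% power; two-sided levels 0.05 and 0.025, where 0.025 = 0.05/2 fits two tests; 126 recruited per group.

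**Assumptions, not in the article.** The 0.025 level is shared between ACIF and PFIT. The effect on PFIT and the ACIF-PFIT correlation are not given, so both are varied. The evaluable number lies somewhere between 35 and 126 per group.

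**1. The plan's own figure.** n per group = 2(z₁₋α/₂ + z₀.₈)²/0.7².
- α = 0.05: 2(1.960 + 0.842)²/0.49 = 32.0, so 33; 34 with the t-test. The stated 35 reproduces within 2 patients.
- α = 0.025: 2(2.241 + 0.842)²/0.49 = 38.8, so 39; 40-41 with the t-test. The stated 35 does not reproduce.

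By the exact t-test, 35 per group and 0.7 SD give 82.3% power at 0.05 and 73.7% at 0.025, a difference of 8.6 points.

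**2. Where Holm gains.** For ACIF, Holm adds a rejection only when the ACIF p-value lies between 0.025 and 0.05 and the PFIT p-value is below 0.025. With 0.7 SD on both and independence:
- ACIF: 0.737 + (0.823 − 0.737) × 0.737 = 0.737 + 0.063 = 0.800.
- Both, Bonferroni: 0.737² = 0.543.
- Both, Holm: both p-values below 0.05 and not both between 0.025 and 0.05, so 0.823² − 0.086² = 0.677 − 0.007 = 0.670.

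**3. With correlation.** Simulated two-sample t-tests, 35 per group, 0.7 SD on both, correlation 0 to 0.7:

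| Quantity | Bonferroni | Holm |
|---|---|---|
| Power for each measure | about 74% | 78-80% |
| Power to claim both | 54-63% | 67-73% |

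The gain of about 4 to 6 points per measure is roughly half to three-quarters of the 8.6 points (4.3/8.6 = 50%; 6.3/8.6 = 73%).

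**4. What does not change.** Holm's first step is Bonferroni's test, so power for at least one claim is identical. With normal test statistics it is 94.0%, 88.4% and 83.5% at correlation 0, 0.5 and 0.8. With no effect on either measure, the simulated family-wise error is also identical: 4.95%, 4.7% and 4.0%.

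**5. How far the gain depends on the assumptions** (normal test statistics, correlation 0 to 0.8):
- PFIT effect 0.35 SD, 35 per group: ACIF gains 0.1 to 1.7 points.
- PFIT effect zero, 35 per group: ACIF gains 0.2 points or less.
- 0.7 SD on both, 63 per group: about 1.4 to 2 points.
- 0.7 SD on both, 126 per group: under 0.1 point (99.95% against 99.98%).

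The weaker measure can gain when ACIF gains little. If PFIT has 0.5 SD at 35 per group, its own power rises from 43% to 51-52% (t-tests, correlation 0 to 0.5).

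**6. If the family is four measures** (0.05/4 = 0.0125 each; normal test statistics, 35 per group). Power per measure goes from 66.7% to 76-78% if all four have 0.7 SD, and to about 69% if only ACIF and PFIT respond.

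**The case against.** The strongest case against is that nothing here is wrong. Bonferroni is valid and conservative, the article does not contradict itself by choosing it, and it has simple matching simultaneous intervals in a plan that reports confidence intervals. That stands: this is an efficiency suggestion. It is still worth making, because the procedure is fixed in the article and Holm gives up no error control and no rejections.

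The second objection is that the two-measure family is assumed. That also stands. The abstract supports ACIF and PFIT, but the primary section adds SF-36 and HADS anxiety, and 0.05/2 could equally stand for physical function and quality of life. The Sample size section also applies 0.025 to mitochondrial DNA, tissue oxygenation and microcirculation. The Bonferroni sentence follows the one on post hoc analyses, so it may cover those comparisons too, although the reason it gives is multiple outcomes. A replacement that named only ACIF and PFIT would therefore leave other tests with no stated correction. The fix has to keep the present family and change only the procedure.

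The third is that the headline gain takes a favourable case: 0.7 SD on both measures and exactly 35 evaluable. The Sample size section does apply 0.7 to physical function outcomes in the plural, so equal effects are the plan's own scenario. But the calculation was made on ACIF, and no separate PFIT effect is given. The 35 is a minimum; 35 of 126 would mean losing 1 − 35/126 = 72%, and the article states no rate. The gain must therefore be shown as conditional.

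**Conclusion.** The point holds as a cheap improvement. Holm gives the same family-wise error control as the planned correction under any correlation and never does worse. In the plan's own scenario it adds about 4 to 6 points of power per measure and about 10 to 13 points for claiming both (73 − 63 and 67 − 54). These figures rest on a family of ACIF and PFIT, 35 evaluable per group, 0.7 SD on both and an assumed correlation of 0 to 0.7.

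A reader might infer three stronger things that the article does not support:
- That Bonferroni is a mistake. It is valid.
- That Holm raises the chance of a positive trial in general. The chance of at least one significant measure is unchanged, and the per-measure gain shrinks if the other measure responds weakly or the evaluable number is well above 35.
- That Holm repairs the sample size. At 0.025, 35 per group gives about 74% power; Holm brings this close to 80% only if both effects are 0.7. That mismatch has to be resolved in the Sample size section.

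**What to change.** In Data Management and Statistical Analysis, replace 'Bonferroni correction' by 'Holm-Bonferroni correction' for every family of tests to which Bonferroni now applies. This includes the post hoc comparisons and any SF-36 and HADS anxiety tests in the primary family. No test should lose its correction through the change.

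State which measures and time points form the primary family. If it is ACIF and PFIT at ICU discharge, add: the smaller two-sided p-value is compared with 0.025 and, if significant, the larger with 0.05. If the family has four members, the ordered p-values are compared in turn with 0.05/4, 0.05/3, 0.05/2 and 0.05, stopping at the first that fails.

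The cost is a few words, settled before unblinding, with no added patients, visits or type I error. Naming the family takes a decision, but the present correction needs that decision too. The one real drawback is that simultaneous confidence intervals are less simple under Holm; report the planned 95% intervals unadjusted and label them so.
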